### Data analysis

The primary analysis will use a generalised linear mixed model with a logit link and a random effect for clinic, allowing for the clustering of participants within clinics. The model will control for the clinic-level baseline antibiotic prescribing rate as well as potential confounders, and the full list of model covariates will be prespecified and set out in the statistical analysis plan. Results will be reported as ORs with 95% CIs.

Missing data will be treated as missing at random and imputed using a chained-equations multiple imputation model. A complete-cases analysis will be presented as a secondary analysis.

The analysis of secondary outcomes will use a similar modelling framework with distributions appropriate to the outcome, for example, linear modelling for continuous outcomes and Poisson/negative binomial for count outcomes. These models will control for clustering and the factors listed above.

All results will be reported in line with the Cluster Randomised Trials extension to the CONSORT (Consolidated Standards of Reporting Trials) guidelines. No interim analyses are planned. Full details of the analyses to be undertaken will be set out in the statistical analysis plan and approved by the Trial Steering Committee (TSC).

### Sample size calculation

Our previous study recorded an antibiotic prescribing rate of 75% for rural township health centres in Anhui province^21 28^ and a previous pilot intervention showed a reduction in antibiotic prescribing of more than 20%.^27^ There is no internationally agreed minimally important difference in antibiotic prescribing, however, we anticipate that a reduction of at least 15% in antibiotic prescribing would represent a meaningful change at the population level given the very high rates of antibiotic prescribing.

To detect a possible absolute difference of 15% in prescribing rates between intervention (60%) and control practices (75%) with 90% power and alpha 0.05, we will need 203 patient consultations for infection RTI in each arm. Based on our previous study results the estimated ICC value was 0.05 and a design effect value would be 2.45. We would, therefore, aim to recruit at least 2.45*203*2=995 patients into the study. Allowing for a loss to follow-up rate of 10% and a cluster size of 30 patients per township health centre, we will recruit 40 township health centres into the study and each arm will have 20 township health centres.

### Economic evaluation

The economic evaluation will be taken from a societal perspective and consider cost implications for patients as well as health services. Resource usage information will be costed using corresponding Chinese tariff.

All itemised resource usage data will be costed using appropriate data, with unit costs of visiting healthcare facilities based on medical service price items. Medication based on clinical consultation patient questionnaire and phone interviews with the patients at 7, 14 and 21 days; and the time spent costed at average wage in Anhui province. Insurance coverage will be weighted to calculate private spending.

Resource use will be weighted by its unit cost over the study period. Accumulated costs per patient will be calculated for the study period. Quality of life data will be translated into a utility score using a Chinese tariff. Quality-adjusted life-years (QALYs) will be estimated using the area under the curve approach.

Missing data will be handled by multiple imputation methods. Difference in costs and QALYs will be compared using a generalised linear mixed model taking clinic as cluster level and by adjusting baseline clinical and quality of life variables. Bootstrapping methods will be used to estimate the incremental cost per QALYs gained and per percentage reduction of antibiotic prescribing. Major assumptions will be explored through sensitivity analyses. Completed cases analyses will be presented as one of such scenario analyses.

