**Methods and analysis:**

A cluster randomised controlled trial will be carried out to estimate the effectiveness and cost effectiveness of a complex intervention in reducing antibiotic prescribing at township health centres in Anhui Province, China. 40 Township health centres will be randomised at a 1:1 ratio to the intervention or usual care arms. In the intervention group, practitioners will receive an intervention comprising: (1) training to support appropriate antibiotic prescribing for RTI, (2) a computer-based treatment decision support system, (3) virtual peer support, (4) a leaflet for patients and (5) a letter of commitment to optimise antibiotic use to display in their clinic. The primary outcome is the percentage of antibiotics (intravenous and oral) prescribed for RTI patients. Secondary outcomes include patient symptom severity and duration, recovery status, satisfaction, antibiotic consumption. A full economic evaluation will be conducted within the trial period. Costs and savings for both clinics and patients will be considered and quality of life will be measured by EuroQoL (EQ-5D-5L). A qualitative process evaluation will explore practitioner and patient views and experiences of trial processes, intervention fidelity and acceptability, and barriers and facilitators to implementation.

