## Introduction

Antimicrobial resistance (AMR) specifically refers to the evolution of drug-resistant micro-organisms, including bacteria, which is driven by high rates of antibiotic use and is a pressing problem for global health and development.^1–3^ If resistance continues to increase, common bacterial infections will eventually become untreatable.^4 5^

Since 2009, China has implemented the national essential medicines scheme and zero-mark-up policies to try to reduce inappropriate antibiotic use.^6 7^ In 2012, the Chinese Ministry of Health issued a regulation to limit antibiotic prescribing to 20% of outpatient prescriptions in all patients.^8^ However, the antibiotic prescribing rate in healthcare facilities in less developed or rural areas remains as high as 80%.^9–14^

In China, patients can choose to go to the outpatient department of any health facility without a referral letter,^15^ however, rural residents mainly seek healthcare from township health centres or village clinics, the two lowest-level health facilities in China’s rural healthcare system. If patients develop severe symptoms, they are more likely to go directly to the outpatient clinic in the county hospital.^15 16^ Many patients attend village clinics and township health centres with respiratory tract infections (RTIs) such as common cold, sore throat, and acute bronchitis and are frequently prescribed antibiotics even though most cases are likely to be viral and antibiotics are therefore unnecessary^17–20^ Our previous study found that the antibiotic prescribing rate for RTI patients was up to 85% in rural Anhui Province.^21^ In addition to the implications for AMR, there is a cost to patients^22 23^ for extra health resource utilisation (consultation fees, medication costs, loss of productivity costs), most of which would not be reimbursed through national medical insurance schemes. Therefore, reducing antibiotic prescribing in village clinics and township health centres is likely to be both safe and economically beneficial to patients. Since the start of the COVID-19 pandemic, village clinics have periodically been prohibited from providing treatment to RTI patients; therefore, this trial focuses on provision of care in township health centres.

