The researcher will conduct telephone interviews with recruited RTI patients at 7, 14, 21 days after their consultation. Structured questionnaires will be completed for each patient by the researcher during the telephone interview, with different secondary outcome data collected at different time points (see table 1). Illness severity (scored on a 10-point scale) and symptom duration will be recorded at each time point. Patient attitude, understanding of the patient leaflet and beliefs will be recorded once at 7 days after consultation (online supplemental appendix 8). Patient continuing illness severity and recovery situation (when they feel better and when they feel they could get back to normal) will be checked at 7 days (online supplemental appendix 8, and 14 days after consultation (online supplemental appendix 9). Patient consumption of antibiotics (including name, days, dosage and quantity) will be recorded at 7, 14 and 21 days after consultation (online supplemental appendix 10). Through checking with patient’s actual consumption of antibiotics (how many days they have taken the antibiotics, dosage etc) at different periods against the prescribed quantity of antibiotics (if applicable), patient adherence to follow practitioner’s advice (%) could be estimated. Other healthcare use (clinic visits or consumption of other treatment) will be recorded at 21 days after consultation. Patient out-of-pocket spending due to this illness, including purchase of medication, fees for clinic attendance, days off-work, will be recorded at 21 days after consultation. Patient quality of life will be measured using the EQ5D-5L during the initial consultation, at 7, 14 and 21 days after consultation. (Use of paper interview administration mode of EQ5D-5L in Chinese version has been authorised by EuroQol Group (registration ID: 32880).

10.1136/bmjopen-2020-048267.supp8Supplementary data

10.1136/bmjopen-2020-048267.supp9Supplementary data

10.1136/bmjopen-2020-048267.supp10Supplementary data

**Table 1 T1:** List of the primary and secondary outcome measures and when they will be collected at follow-up audit

Item	Outcome measure	Initial consultation	Patient telephone interview after consultation		
			7 days	14 days	21 days
Primary outcome	Prescribing rate of antibiotics (%)	√			
Secondary outcomes	Patient satisfaction	√			
	Patient symptom severity and duration		√	√	√
	Patient recovery		√	√	
	Patient consumption of antibiotics		√	√	√

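### The bootstrapped cost-per-QALY ratio is likely to be unstable over a 21-day horizon; net monetary benefit should be the main cost-per-QALY summary

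*Protocol article*

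**What the plan says.** The abstract sets the time frame: "A full economic evaluation will be conducted within the trial period". Under Data collection methods, "Patient quality of life will be measured using the EQ5D-5L during the initial consultation, at 7, 14 and 21 days after consultation", and Table 1 shows the same schedule. The Economic evaluation section then states that "Quality-adjusted life-years (QALYs) will be estimated using the area under the curve approach" and that "Difference in costs and QALYs will be compared using a generalised linear mixed model taking clinic as cluster level", with adjustment for baseline clinical and quality-of-life variables. The next sentence gives the two summary measures: "Bootstrapping methods will be used to estimate the incremental cost per QALYs gained and per percentage reduction of antibiotic prescribing".

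The article states no expected QALY difference. The nearest it comes is in the Introduction, which holds that "most cases are likely to be viral and antibiotics are therefore unnecessary" and that "reducing antibiotic prescribing in village clinics and township health centres is likely to be both safe and economically beneficial to patients". It does not say what will be reported if the QALY difference is close to zero or negative.

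On costs, the section takes a societal perspective covering patients and health services, and says: "All itemised resource usage data will be costed using appropriate data, with unit costs of visiting healthcare facilities based on medical service price items". It then gives sources for medication and for time.

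**The concern.** A cost-per-QALY ratio divides by the QALY difference. The result the trial hopes for is fewer antibiotics, lower cost and no harm, which puts that denominator near zero. Bootstrap draws then fall on both sides of zero and the ratio jumps between large positive and large negative values. Its sign also stops being informative. A negative ratio arises when the intervention is better and cheaper, and equally when it is worse and dearer. A positive ratio arises when it is better and dearer, and equally when it is worse and cheaper. Percentiles of such a mixture have no clear meaning.

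At stake is the cost-per-QALY part of the value-for-money evidence that the Introduction promises for policy. The primary effectiveness analysis is not touched.

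**Working it through.** **The plan's own figures.** The article gives no precision figure for the economic evaluation, so only the sample size can be reproduced. For 75% against 60%, 90% power and two-sided alpha 0.05, the pooled formula gives 203 per arm. The design effect is 1 + (30 − 1) × 0.05 = 2.45, and 2.45 × 203 × 2 = 994.7, or 995. Allowing for 10% loss, 995/0.9 = 1106, or 36.9 centres of 30, which 40 centres cover. These figures agree with the article.

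**Inputs from the article.** EQ-5D-5L at days 0, 7, 14 and 21; 20 centres per arm; 30 patients per centre; 10% loss, hence 27 per centre and 540 per arm.

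**Assumed inputs.** The article gives none of these. SD of a patient's mean utility over the 21 days: 0.05, 0.10 or 0.15. ICC for utility: 0.01 or 0.05 (the article's 0.05 is for prescribing). Utility difference d: zero at day 0 and constant from day 7 to day 21, with d between 0 and 0.05.

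**Formulas.**
- Largest possible QALY per patient: 21/365.25 = 0.0575.
- QALY difference by trapezoids: (3.5 + 7 + 7) × d/365.25 = 17.5 × d/365.25.
- SE = SD × 0.0575 × √[(2/540) × (1 + 26 × ICC)]. At SD 0.10 and ICC 0.05 this is 0.10 × 0.0575 × √(0.003704 × 2.3) = 0.00053. Over all six SD and ICC combinations it runs from 0.00020 to 0.00080.
- Share of draws with a denominator at or below zero: Φ(−z), where z = QALY difference/SE.
- The 95% Fieller interval for the ratio is bounded only if |z| > 1.96.

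**Results**, for a trial whose estimate equals the assumed difference:

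| d | QALY difference | z (SD 0.10, ICC 0.05) | Draws ≤ 0, same case | Draws ≤ 0, six cases | Interval unbounded in |
|---|---|---|---|---|---|
| 0 | 0 | 0 | 50% | 50% | 6 of 6 |
| 0.005 | 0.00024 | 0.45 | 33% | 11% to 38% | 6 of 6 |
| 0.01 | 0.00048 | 0.90 | 18% | 0.7% to 27% | 5 of 6 |
| 0.02 | 0.00096 | 1.81 | 3.5% | <0.1% to 11% | 3 of 6 |
| 0.05 | 0.0024 | 4.51 | <0.1% | at most 0.1% | 0 of 6 |

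**The other ratio.** For cost per percentage reduction in prescribing, the planned difference is 15 points. Its SE is √[(0.75 × 0.25 + 0.60 × 0.40)/(600/2.45)] = 0.0418, so z = 0.15/0.0418 = 3.6, and the chance of a denominator at or below zero is 0.0002.

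**Illustration.** Take an assumed cost difference of 20 currency units (SE 10), independent of effect, and 5,000 draws at SD 0.10 and ICC 0.05. With no QALY difference, the 2.5th and 97.5th percentiles of cost per QALY are about −746,000 and 611,000. At d = 0.02 they are about −69,000 and 171,000. Cost per percentage point, with the planned 15-point effect, runs from 0.02 to 3.73.

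**The case against.** The strongest reply is that the economic evaluation does not rest on this ratio. The same sentence plans a second, stable ratio tied to the primary outcome, and the sentence before it compares costs and QALYs separately in a clustered model. Those results stay interpretable whatever the QALY denominator does. This stands: a reader might infer that the whole economic result becomes uninterpretable, and the article does not support that.

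The instability also depends on assumed inputs. This stands too, which is why a range is shown; at a sustained difference of 0.05 the problem disappears. The SE above ignores the planned baseline adjustment, which would normally reduce it. The SD of 0.05 gives some idea of that effect, since halving the SD from 0.10 corresponds to a baseline that explains 75% of the variance (1 − 0.5²). Even then the interval is unbounded at d = 0.005.

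Three further inferences are tempting and are not supported:
- **The ratio is undefined.** It is undefined only at exactly zero. Elsewhere near zero it is unstable.
- **Delivery costs are left out, so the result is biased towards saving.** Training, software, peer and technical support and leaflets are not named among the cost items. However, the societal and health-service perspective, and the stated objective on costs to health centres as well as patients, include them in general terms. A condensed article may leave the itemised list to a fuller document.
- **The bootstrap ignores clustering.** The article does not name the resampling unit, and the sentence before it takes clinic as the cluster level.

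Finally, net benefit, planes and acceptability curves can be produced from the same bootstrap draws, and nothing rules them out. That is true, but the measure the article commits to is the ratio, with no provision for a small or negative denominator.

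**Conclusion.** The point holds for one of the two planned ratios. Over a horizon worth at most 0.0575 QALY, and with an intervention expected to be safe rather than to improve health, the cost-per-QALY ratio is a poor choice of main summary. At SD 0.10 and ICC 0.05, about half the draws are at or below zero with no difference and 18% at a 0.01 utility difference, and the interval stays unbounded up to a difference of about 0.02. With no true difference, the interval would be unbounded in 95% of trials by construction, because it is bounded only when the QALY difference is itself significant at 5%.

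This rests on assumed utility SD, ICC and difference, and on reading a near-zero QALY difference into the Introduction's safety expectation. It does not extend to the prescribing ratio, to the separate cost and QALY differences, or to the primary analysis. The delivery costs are a matter for clarification only.

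**What to change.** Prespecify incremental net monetary benefit (willingness to pay × QALY difference − cost difference) over a stated range of willingness to pay as the main cost-per-QALY summary, with a cost-effectiveness plane and an acceptability curve. It involves no division, so its interval is always finite and its sign has one meaning. Obtain it from the clustered model or from a bootstrap that resamples centres.

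Report the cost-per-QALY ratio alongside it whatever the significance of the QALY difference, since reporting it only after a significant result would invite selective reporting. Keep the cost per percentage reduction in prescribing and the separate cost and QALY differences as planned.

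As a clarification, add a sentence confirming that the costs of training, software, support and leaflets are counted under the stated perspective.

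No new patient data are needed. The price is a little more analysis, the need to justify a willingness-to-pay range, and a headline measure less familiar to some readers.

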### Qualitative process evaluation

A Mandarin-speaking qualitative researcher will conduct observations of the training process and intervention implementation. The key content related to participants during the training process, including any additions by the trainer, questions and answers, comments or discussion among participants and non-verbal reactions displayed by participants will be recorded. The researcher will visit intervention clinics and observe how the intervention is being implemented.

A Mandarin-speaking qualitative researcher will conduct semistructured interviews with the intervention practitioners. Short interviews will be conducted at the end of the training, to elicit intervention practitioners’ views about the training. After intervention practitioners have had time to implement the intervention in their clinics, they will be invited to participate in a second semi-structured interview to understand their experiences of the intervention. They will be asked to describe how they used the intervention in their practice, any barriers and facilitators encountered in following the intervention and whether it influenced their views or practice.

A purposive sample of up to 40 patients who are recruited into the study will be interviewed. Patient will be selected to capture a range of sociodemographic characteristics and illness presentations. Some will be interviewed immediately after completing their consultation with health practitioners and some after they have completed the telephone questionnaires. Interviews will be semistructured and guided by a topic guide that will cover experience of the consultation and understandings of the patient leaflet they received.

All semistructured interviews will be transcribed. The qualitative data will be analysed thematically.

### Data handling and repository

This trial will be monitored by a TSC and collected data will be monitored by data monitoring committee. There are no anticipated risks to patients from taking part in the study and participants have the right to withdraw from the study at any time without giving a reason.

Hard copies of documents with identifiable details of patient, practitioner and clinic will be stored in lockable cabinets on premises approved by the principal investigator or relevant co-investigators at Anhui Medical University and any data created will be encrypted and stored on University secure servers until they can be uploaded or scanned and stored in the University of Bristol Research Data Storage Facility (RDSF) at the first available opportunity. Only authorised users can access data stored within the RDSF and procedures will be put in place to allow authenticated, external collaborators to view add and/or edit data.

When possible, data will be exported directly to databases and consistency maintained via peer review and cross-checks with previous measurements. Manually inputted data will be double entered. Quality of questionnaire and interview data will be assured by training, provision of an interview manual and resurvey of 5% of subjects.

### Patients and public involvement

Patients (and practitioners) contributed to the co-design of the intervention. They also provided feedback on piloted data collection forms, which led to modifications. The results will be disseminated to study participants and other stakeholders. At the end of the research project we will hold a high-level meeting to disseminate our findings to key stakeholders and develop a strategy for impact with relevant stakeholders.

## Ethics and dissemination

Ethical approval was obtained from the Biomedical Research Ethics Committee of Anhui Medical University (Ref: 20180259); the study has undergone due diligence checks and is registered at the University of Bristol (Case No: 2020-3137). This project is one of the three work packages in the UK-China AMR Centre Partnerships 2018 (Strategies to reduce the burden of antibiotic resistance in China) supported by UKRI (UK Research and Innovation) Medical Research Council (Grant Ref: MR/S013717/1)) and National Natural Science Foundation of China (Grant Ref: 81861138049). The protocol is rooted in a multidisciplinary collaboration between institutions in the UK and China.

Throughout the research project we will involve key stakeholders with roles in managing antibiotic use and AMS. Research findings will be translated into short policy briefings with recommendations informed by existing policies in China and to influence current practice in healthcare settings. The credibility of research findings will be indicated to stakeholders through peer-reviewed publications in internationally recognised journals and presentations at academic conferences in China, the UK and internationally.
